##### Side effects associated with solifenacin

The side effects induced by Solifenacin will be recorded in the CRF, including dry mouth, dry eyes, and constipation.

##### Adverse events

Except from the side effects induced by EA, SA, and solifenacin, all other adverse events will be recorded in the CRF throughout the trial, and their relationships with the intervention and controls will be assessed.

#### Adherence assessment

The sessions of treatments will be recorded in the CRF to assess the adherence of patients.

### Data management

The CRF will be filled in before the input of data into the Electronic Data Capture (EDC) System, which will be developed by a third independent corporation (Linkermed Technology Co. Ltd). The database will be protected by a password and only the principal investigator will have access to the final dataset.

The EDC system will be locked once the study is completed. The CRF and dataset will be preserved for 5 years. Data from the trial will be shared upon request to the corresponding author anonymously, excluding the private information of patients.

### Statistical analysis

For the primary hypothesis, we will compare the decrease in UUI episodes among the three groups. A decrease in number will indicate less incontinence. Additionally, we will use a modified *t*-test based on the retention of effect method to analyze whether EA is noninferior to solifenacin [21]. In detail, to establish the assay sensitivity of the trial, a *t*-test investigating the superiority of solifenacin over SA will be performed first by comparing the decrease in the number of UUI episodes in the solifenacin and SA groups. After superiority has been established, a modified *t*-test will be used to assess whether the difference in the numbers between the EA and SA groups is more than 50% of the mean difference between the numbers in the solifenacin and SA groups. An appropriate Fieller’s confidence interval can also be provided [21]. If the *P* Value is equal to or less than 0.025 or if the lower boundary of the confidence interval around the mean difference between the numbers in the EA group versus that in the solifenacin group exceeds this value, then noninferiority will be established. After the noninferiority assessment, traditional *t*-tests will be used for superiority analyses, including a decrease in the number of UUI episodes for solifenacin versus EA, and EA versus SA.

A mixed-effect model or Wilcoxon rank-sum test will be used to assess the longitudinal continuous variables. A generalized linear model or logistic regression will be performed to assess the rates of response. Chi-square or Fisher’s exact tests will be used to compare the frequency of AEs between groups.

Primary outcome analysis will be performed in the intention-to-treat (ITT, randomized participants) and per-protocol datasets (PP, ITT participants who received at least one treatment session without major violation of the protocol). Missing data will be imputed using the multiple imputation method under the missing-at random assumption. Secondary and safety outcomes will be assessed in ITT populations.

Since all analyses other than the primary analysis are considered descriptive, no adjustments will be made for multiple testing, and *P* values should be interpreted accordingly. Analyses will be performed using SAS version 9.4 (SAS Institute Inc) with a two-sided *P* value of less than .05 considered significant.

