**Fig. 1 Fig1:**
[figure not shown]
Study Flowchart. *The dose of solifenacin can be increased to 10 mg per day and can be discontinued following a comprehensive consideration of the state of incontinence symptoms and the side effects

**Table 1 Tab1:** Outcome Assessment Schedule

The assessment of timepoint						
Timepoint	Week 0	Week 4	Week 8	Week 12	Week 24	Week 36
Incontinence episodes in 72 h	X	X	X	X	X	X
Urgency incontinence episodes in 72 h	X	X	X	X	X	X
Stress incontinence episodes in 72 h	X	X	X	X	X	X
Other incontinence episode in 72 h	X	X	X	X	X	X
Urinary frequency in 72 h	X	X	X	X	X	X
Urinate episodes regarded as Grade 2 by PPIUS* in 72 h	X	X	X	X	X	X
Urinate episodes regarded as Grade 3 by PPIUS in 72 h	X	X	X	X	X	X
Nocturia episode in 72 h	X	X	X	X	X	X
Water input in 72 h	X	X	X	X	X	X
Pad consumption in 72 h	X	X	X	X	X	X
ICIQ SF* questionnaire	X	X	X	X	X	X
OAB-q SF* questionnaire	X	X	X	X	X	X
PGI-I* score				X		X
PGSC*		X	X	X	X	X
Expectance evaluation	X					
Blind effect evaluation				X		
Dose of solifenacin taken		X	X	X	X	X
Safety evaluation of acupuncture	X					
Adverse effect of Solifenacin	X					
Other adverse events	X					
Combination of medication	X					
Adherence evaluation	X					
Completeness of research	X					

Abbreviations: PPIUS: Patient perception of Intensity of Urgency Scale; ICIQ SF: International Consultation on Incontinence Questionnaire Short Form; OAB-q SF: Overactive bladder questionnaire short form; PGI-I: Patient global impression improvement; PGSC: Patient Global Symptom Control

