#### Randomization

Randomization will be performed by an independent third party, Linkermed Technology Co. Ltd. (Beijing, China). Randomization sequence will be generated by computers in varying block sizes and stratified by centers, and central randomization system will be adopted to conduct the process. Once the patient is confirmed eligible to be enrolled, the study coordinator in charge of the randomization will log into the central randomization system to obtain the allocation information. Patients will be randomly allocated into the EA group, SA group, or solifenacin treatment group at a ratio of 1:1:1.

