### Measures

#### Outcome assessment

##### Primary outcome measure

The primary outcome is the change in UUI episodes during an average 24-h period at 12 weeks from the baseline (after the first treatment), recorded in a 3-day voiding dairy.

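### The primary t-tests on the decrease in UUI episodes are valid, but they lose precision by fixing the baseline slope at 1 and leaving out centre, the stratification factor

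*Protocol article*

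**What the plan says.** The endpoint is a change score. The article defines it thus: "The primary outcome is the change in UUI episodes during an average 24-h period at 12 weeks from the baseline".

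The Statistical analysis section announces that "we will compare the decrease in UUI episodes among the three groups". It then names the test for each primary step:

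- Assay sensitivity rests on an ordinary two-sample t-test, described as "investigating the superiority of solifenacin over SA will be performed first by comparing the decrease in the number of UUI episodes". The two arms involved are solifenacin and SA.
- Non-inferiority rests on a t-test modified for retention of effect, which (in the words of the article) "will be used to assess whether the difference in the numbers between the EA and SA groups is more than 50% of the mean difference". The reference is the solifenacin-SA difference, and a Fieller interval is an option.
- Afterwards come traditional t-tests, which (again in its words) "will be used for superiority analyses, including a decrease in the number of UUI episodes for solifenacin versus EA, and EA versus SA".

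No covariate is named for any of these. The only model named for continuous data is in a separate sentence: "A mixed-effect model or Wilcoxon rank-sum test will be used to assess the longitudinal continuous variables". That sentence is not tied to the primary test, offers a rank test as the alternative and lists no covariates.

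Both candidate covariates are already available. Table 1 lists "Urgency incontinence episodes in 72 h" at week 0 and at every later visit. The Randomization section says: "Randomization sequence will be generated by computers in varying block sizes and stratified by centers". The Patient recruitment section names six hospitals.

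**The concern.** This is not a detail left to a later analysis plan. The article fixes the primary method test by test, and an analysis plan that follows it would run unadjusted t-tests.

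Two sources of avoidable variance follow. First, the decrease is likely to depend on the starting count: entry requires four or more UUI episodes over three diary days with no upper limit, and nobody can fall below zero. A change score assumes that each extra baseline episode carries through in full to week 12. Where the real slope differs from 1, the mismatch stays in the residual variance. Second, stratified randomisation balances the arms within centres. Between-centre variation therefore hardly affects the arm contrasts, yet an unstratified t-test still counts it in the standard error.

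The retention test is where precision matters most. It is the contrast EA - 0.5 x solifenacin - 0.5 x SA. If EA equals solifenacin and both exceed SA by D, the contrast is 0.5D with variance factor 1.5/n. The solifenacin-SA test has signal D and factor 2/n. For equal power, the required n per arm is in the ratio (1.5/0.25)/(2/1) = 3. The main claim of the trial rests on the more demanding of these two tests.

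**Working it through.** **The plan's own figure.** Recruitment adds up: 42 + 5 x 48 = 282 = 3 x 94. With the stated 10% drop-out, 94 x 0.9 = 84.6 evaluable per arm. The 94 itself cannot be derived, because the Sample size calculation section prints no effect, SD or power. Nothing below depends on how it was obtained.

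**Assumed inputs (not in the article).** Correlation r between baseline and week-12 UUI; ratio k of week-12 SD to baseline SD; 80% power for the unadjusted retention test.

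**Variance.** With baseline SD s, the change-score variance is s²(1 + k² - 2rk) and the baseline-adjusted residual variance is s²k²(1 - r²). The difference is s²(1 - rk)². It is never negative, and it is zero only when the true slope rk is 1. For k = 1 the ratio of adjusted to unadjusted variance is (1 - r²)/(2(1 - r)) = (1 + r)/2.

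**Power.** At 80% power and one-sided 0.025 the standardised signal is 1.960 + 0.842 = 2.802, so power after adjustment is Phi(2.802/sqrt(ratio) - 1.960).

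| r (k = 1) | Variance ratio | Evaluable per arm for the same precision (84.6 x ratio) | Power instead of 80% |
|---|---|---|---|
| 0.3 | 0.65 | 55.0 | 93.5% |
| 0.5 | 0.75 | 63.4 | 89.9% |
| 0.7 | 0.85 | 71.9 | 86.0% |
| 0.9 | 0.95 | 80.4 | 82.0% |

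The degrees of freedom spent (one for baseline, five for six centres, out of about 250) take these powers down by up to about 1 point.

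**Unequal SDs.** For k = 0.8 the ratio k²(1 - r²)/(1 + k² - 2rk) lies between 0.50 and 0.64 over r = 0.3 to 0.9. At r = 0.5, for example, it is 0.48/0.84 = 0.571. In the other direction, r = 0.9 with k = 1/0.9 = 1.11 gives rk = 1 and no gain.

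**Simulation of the retention contrast** (85 per arm, six centres, normal data, 4,000 replicates). At r = 0.5, power was 79.9% unadjusted and 89.5% adjusted. When centre explained 5% of the variance of the change, it was 80.3% and 91.2%, and the variance ratio moved from 0.753 to 0.721. Over r = 0.3 to 0.9, with and without a centre effect, one-sided type I error was 0.021 to 0.029 unadjusted and 0.022 to 0.027 adjusted. This is compatible with 0.025 at a simulation standard error of sqrt(0.025 x 0.975/4000) = 0.0025.

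**Pooled variance in the retention test.** The contrast weights 1, -0.5, -0.5 are unequal, so equal arm sizes do not protect a pooled-variance test. With variances v, the true factor is v(EA) + 0.25 v(solifenacin) + 0.25 v(SA), and the pooled factor is 1.5 x the mean of the three. One-sided error is 1 - Phi(1.96 x sqrt(pooled/true)):

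- EA variance doubled: pooled 2.0, true 2.5, error 0.040.
- EA variance halved: pooled 1.25, true 1.0, error 0.014.
- Solifenacin variance doubled: pooled 2.0, true 1.75, error 0.018.

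**The case against.** The strongest reply is that nothing here is an error. The t-tests are valid, the simulated type I error stays near 0.025, and omitting centre tends to make a test conservative. The retention test with its Fieller interval follows a cited method. On this view, preferring adjustment is a recommendation and not a correction. That stands, and the point is put as one of efficiency.

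Four stronger readings are tempting, and the article does not support them.

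- *The tests ignore baseline, so any chance imbalance passes straight into the result.* The change score already subtracts baseline. With equal SDs only the fraction 1 - r of an imbalance remains: half at r = 0.5, a tenth at r = 0.9. It averages to zero over randomisation and is already reflected in the standard error.
- *The trial is short of precision.* No effect, SD or power is printed, and the 50% margin is named in the sample size section itself, so 94 per arm may already allow for the harder contrast. The factor of 3 shows which test is more demanding, not that it is underpowered.
- *The gain is large.* It may be, but at r = 0.9 with equal SDs it is 2 points of power, and it vanishes when the true slope is 1. The floor at zero and the entry threshold make equal SDs doubtful. The counts are probably skewed, while the simulation used normal data.
- *The retention test has inflated error.* The article does not say that the variance is pooled. If it is, the error can fall on either side of 0.025, as the three cases show.

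What remains is that a fixed slope of 1 and an omitted stratification factor cannot improve large-sample precision and will usually reduce it, while both variables are already recorded.

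**Conclusion.** The point holds as a recommended improvement. Every primary step is fixed as an unadjusted t-test on the decrease, and nothing else in the article supplies an adjustment for baseline or centre. The inference is valid but usually less precise than the same data allow.

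Under equal SDs the excess is (1 - r)/2 of the change-score variance: 35%, 25%, 15% and 5% at r = 0.3, 0.5, 0.7 and 0.9. The direction is secure. The size is not, because r, the SDs and the planned power are all assumptions here. Centre probably adds a smaller gain: about 3 points of variance ratio at r = 0.5 if it explains 5% of the variance. A reader should infer neither bias, nor inflated type I error, nor an undersized trial.

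**What to change.** Name one linear model as the primary analysis: week-12 UUI episodes per 24 h (or, equivalently once baseline is included, the change) on arm with three levels, baseline UUI and centre. Take every contrast from it:

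- solifenacin - SA, for assay sensitivity;
- EA - 0.5 x solifenacin - 0.5 x SA at one-sided 0.025, for retention of effect, with signs set so that larger means more improvement;
- EA - SA and EA - solifenacin, for the later superiority tests.

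Build the Fieller interval from the model's estimates and covariance matrix. The retention test is a linear contrast of three means, so the 50% hypothesis, the alpha level and the testing order stay as they are. A heteroscedasticity-robust covariance is a sensible safeguard against unequal arm variances. Keep the unadjusted t-tests as sensitivity analyses.

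The Trial status section says that recruitment has begun, so this needs a dated amendment, made before anyone sees unblinded data. Beyond that, the cost is about six degrees of freedom out of about 250. No new data are needed.

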## Methods and analysis

### Study design

The study will be a multicentered, randomized, three-armed, non-inferiority clinical trial with sham electroacupuncture (SA) and solifenacin as controls. The null hypothesis is that the improvement (difference in the number of UUI episodes between baseline and 12-week assessment) in the EA group would be 50% or less of the difference in improvement between the solifenacin and SA groups; that is, noninferiority would be established if EA, compared with solifenacin, retains at least 50% of the efficacy of solifenacin over SA. The outcome assessors and statisticians will be blinded. Patients in the EA and SA groups will be blinded, while those in the solifenacin group will not be blinded. The study will be carried out after the ethics is approved by the Institutional Review Board. All the patients in the study will be informed about the details of the study and written informed consent will be obtained before enrollment.

In the written informed consent, the participants will be informed that if they are eligible and willing to participate in the study, they will be randomized into the EA group, SA group, or solifenacin group with the same probability. The investigators plan to enroll 282 participants, with 94 in each group. Solifenacin is an effective treatment for the UUI component, as recommended by the current guidelines, and our previous studies indicated that EA and SA are both effective for urgency-predominant MUI to some degree. In the EA group, participants will receive traditional EA at traditional acupoints, while participants in the SA group will receive shallow and minimal EA at non-acupoints.

The study is designed and reported in accordance with the Consolidated Standards of Reporting Trials (CONSORT) guidelines, the Standard Protocol Items: Recommendations for Interventional Trials (SPIRIT) Checklist, and Standards for Reporting Interventions in Controlled Trials of Acupuncture (STRICTA) recommendations. The protocol has been reviewed, revised, and supported by experts in statistics, urology, and acupuncture.

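### The confidence-interval route to non-inferiority is built on EA minus solifenacin against an undefined threshold, so it does not match the 50% retention contrast that the modified t-test examines

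*Protocol article*

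**What the plan says.** **Study design, protocol article.** The null is that the improvement "in the EA group would be 50% or less of the difference in improvement between the solifenacin and SA groups". The same sentence then restates the aim: non-inferiority holds if EA "retains at least 50% of the efficacy of solifenacin over SA".

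**Statistical analysis.** Larger values favour a treatment, because the outcome is a reduction in episodes ("A decrease in number will indicate less incontinence"). Solifenacin must first beat SA. A modified t-test then asks "whether the difference in the numbers between the EA and SA groups is more than 50% of the mean difference" between solifenacin and SA. A ratio-scale interval is optional: "An appropriate Fieller’s confidence interval can also be provided".

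The success criterion follows. It begins "If the *P* Value is equal to or less than 0.025 or if the lower boundary" and continues with "the confidence interval around the mean difference between the numbers in the EA group versus that in the solifenacin group exceeds this value". The section closes by setting the general level, "with a two-sided *P* value of less than .05 considered significant".

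**The concern.** Non-inferiority of EA is the aim given in the Discussion, and the Statistical analysis section treats everything outside the primary analysis as descriptive. The success criterion therefore has to be unambiguous, and it is not.

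- **Different parameter.** The test examines a contrast of three arms. The interval is for a difference of two arms.
- **Undefined threshold.** The value to be exceeded could be 0.025, which stands just before it, or 50% of the solifenacin–SA difference. No sign is given.
- **The matching interval is unused.** Fieller's interval for the ratio belongs to the retention hypothesis, but no decision is attached to it.
- **Inconsistent null.** The first clause in Study design compares EA's own improvement, without subtracting SA, with half of the solifenacin–SA difference.

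At stake is whether the reported interval supports or contradicts the reported P value, and whether the one-sided error stays at 0.025.

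**Working it through.** **Inputs from the article.** 94 per arm (282/3; the centre targets agree, 42 + 5 × 48 = 282), 10% drop-out, 50% retention, level 0.025. 94 × 0.9 = 84.6, so n = 85 evaluable per arm is used.

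**Assumptions.** The article gives no SD, effect size or power. I take a common SD s = 1 and solifenacin − SA = 0.744, the value at which the retention contrast has 80% power at n = 85. Write E, R and P for the mean reductions with EA, solifenacin and SA. Normal approximation throughout.

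**Step 1. The modified t-test.** E − P > 0.5(R − P) is the same as C = E − 0.5R − 0.5P > 0.
- Var(C) = (1 + 0.25 + 0.25)s²/n = 1.5/85, SE 0.1328. Success needs C > 1.96 × 0.1328 = 0.260.
- Error at exactly 50% retention: 0.025.
- Power when E = R: Φ(0.372/0.1328 − 1.96) = 0.80.

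**Step 2. The interval criterion taken alone.** SE(E − R) = √(2/85) = 0.1534, so the half-width of a 95% interval is 0.301.

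| Reading of the threshold | Condition | Pass rate when E = R |
|---|---|---|
| +0.5 × observed (R − P) | E − 1.5R + 0.5P > 0.301, variance 3.5/85 | Φ((−0.372 − 0.301)/0.203) = 0.0005 |
| 0.025 (taken in SD units) | E − R > 0.025 + 0.301 | Φ(−0.025/0.1534 − 1.96) = 0.017 |
| −0.5 × observed (R − P) | C > 0.301 | Φ((0.372 − 0.301)/0.1328) = 0.70 |

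The last reading has the right boundary but the wrong standard error. Its error at 50% retention is 1 − Φ(1.96 × √(2/1.5)) = 0.012.

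**Step 3. Disagreement.** Under the −50% reading, test and interval differ when C lies between 0.260 and 0.301. When E = R the chance is 0.80 − 0.70, about 10% (simulation including the solifenacin > SA step: 9.5%).

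**Step 4. What the 'or' does.** A C above 0.301 is always above 0.260. Once R > P has been shown, the other two readings are stricter than the −50% one. So with equal variances, a 95% interval and the margin estimated in the trial, the interval never passes where the test fails. Simulation (2,000,000 trials) found no such case: the combined rule kept error 0.025 and power 0.80.

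**Step 5. Where the nesting fails** (true retention exactly 50%, nominal one-sided error 0.025):
- *SA more variable, −50% reading, each rule using its own arms' variances.* With an SA SD of k, Var(C) = (1.25 + 0.25k²)/n, which exceeds 2/n when k > √3 = 1.73. At k = 2 the error is 1 − Φ(1.96 × √(2/2.25)) = 0.032.
- *90% interval, −50% reading.* The half-width is 1.645 × 0.1534 = 0.252, below 0.260. The error is 1 − Φ(1.645 × √(2/1.5)) = 0.029.
- *Fixed planning margin of 0.372 SD.* By simulation the combined error is about 0.036 if the true R − P is 0.744 SD, and about 0.094 if it is 0.45 SD.

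**Step 6. The first clause of the null.** Literally it reads E ≤ 0.5(R − P). Illustrative means: with P = 1.0, R = 1.6 and E = 1.0, 1.0 > 0.3, so an EA arm equal to sham lies outside the null. With P = 0.2, R = 1.6 and E = 0.2, 0.2 < 0.7, so it lies inside. EA equal to sham escapes the literal null only if SA's own improvement exceeds half of the solifenacin–SA difference. The article gives no size for SA's improvement.

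**The case against.** The strongest reply is that a correct confirmatory test is already specified: the assay-sensitivity step, the retention contrast and the 0.025 level are all there. Since 'or' joins the criteria, failing the interval cannot overturn a passed test. Under the natural conditions the interval adds no successes either. Step 4 confirms this.

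A reader might therefore infer too much in three places.

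- **That the trial's power falls to 70%, or below 0.1%.** Those are pass rates of the interval criterion alone. The article does not make it the sole criterion.
- **That the wording leaves a useful choice open after unblinding.** Under the conditions of Step 4 nothing is gained by choosing, because the interval never passes where the test fails.
- **That Study design sets up a rival hypothesis which sham-equivalent EA would satisfy.** The same sentence goes on to state retention of 50% of the solifenacin effect, and no analysis compares EA's raw improvement with half of the solifenacin–SA difference. This is a wording fault.

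The reply does not rescue the interval criterion itself, since no reading of it equals the modified t-test. The conditions that make it harmless are also not all secured. The criterion gives no confidence level, although 0.025 and the two-sided .05 point to 95%. Equal variances are not stated. The Discussion argues against external margins, but the criterion does not say that its threshold is the in-trial one.

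Nor is this detail that can simply be left to an analysis plan. The article states the success rule, and a plan that settles it would have to depart from part of the published text.

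**Conclusion.** The point holds in limited form. The interval criterion concerns the wrong parameter and an undefined threshold, and it can contradict the modified t-test on the same data. Under the most favourable reading this happens in about 10% of trials when EA equals solifenacin (n = 85 per arm, solifenacin − SA = 0.744 SD, both assumed).

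With equal variances, a 95% interval and the in-trial margin, the stated rule keeps error 0.025 and power 0.80. The harm is then an interval that does not support the declared conclusion. Error rises above 0.025 only in settings that the wording does not firmly exclude: about 0.029 with a 90% interval, 0.032 with an SA SD twice the others, and 0.036 to 0.094 in the fixed-margin cases tried. These figures are illustrations on assumed effects and are not properties of the trial as planned.

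The opening clause of the null is a separate, smaller inconsistency with the clause that follows it.

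**What to change.** In Study design and Statistical analysis, and in the analysis plan, state one null: H0: (EA − SA) ≤ 0.5 × (solifenacin − SA), tested only after solifenacin has been shown superior to SA.

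State one rule: one-sided P ≤ 0.025 for EA − 0.5 × solifenacin − 0.5 × SA. Once the first step is passed, this is equivalent to the lower limit of the two-sided 95% Fieller interval for (EA − SA)/(solifenacin − SA) lying above 0.5, provided both use the same variance estimate.

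Delete the 'or' and the EA-versus-solifenacin interval criterion. Report that difference with its interval as description only.

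The cost is a short text amendment, with no new data and no change to the sample size. Recruitment has started, so the change should be made and dated before unblinding.

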### Subjects

#### Sample size calculation

The sample size was calculated based on our previous study [10]. The expected drop-out rate is 10% and the noninferiority margin is 50% of the comparative efficacy between SA and Solifenacin. The noninferiority margin was set based on our hypothesis that EA will be associated with at least 50% of the difference in the efficacy of solifenacin as compared with that of SA.

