##### Secondary outcomes

UUI episodes, urinary frequency, urgency, nocturia, pad consumption, and volume drunk in an average 24-h period will be recorded in a 3-day voiding diary both during the treatment period (week 4, week 8, week 12) and the follow-up period (week 24, week 36). The 3-day voiding diary is a reliable, objective, and sensitive measurement recommended by EAU guidelines to monitor changes in incontinence. Urination, urgency, incontinence, drinking, and pads consumed are recorded. Urgency will be evaluated using the Patient Perception of Intensity of Urgency Scale (PPIUS), which is recommended by the European Medicines Agency [14]. Voiding at levels of 3 and 4 are regarded as urgency episodes [15], while levels 1 and 2 are regarded as normal or a strong desire to void [14].

In addition, the ICIQ SF and OAB-q SF scores will be applied as outcome measurements both during the treatment period (week 4, week 8, week 12) and follow-up period (week 24, week 36). The ICIQ SF is a questionnaire developed by the International Consultation on Incontinence [16] to evaluate the severity of incontinence and impact on QoL in the past 4 weeks. It contains four items: frequency, amount of leakage, impact of UI on QoL, and a separate item to indicate the cause of incontinence. The score is the sum of the first three items and the total score ranges from 0 to 21, with a higher score indicating worse symptoms and greater impact on QoL. A Chinese version has been translated and validated [17]. OAB-q SF is a validated questionnaire used to assess the burden of OAB symptoms and the effect on QoL in the past 4 weeks. The questionnaire includes items on coping, sleep, and emotional interactions [18]. The scores are transformed to a 0- to 100-point scale, with higher symptom-severity scores indicating worse symptoms and higher QoL scores indicating a better QoL. A Chinese version of OAB-q SF has also been validated [19].

Patient global impression improvement (PGI-I) will be applied in week 12 and week 36 to measure the effects of therapy subjectively. PGI-I is a scale ranging from 1 to 7, with 1 indicating very much better, 2 indicating much better up to 7 indicating very much worse [20].

Residual urinary volume will be retested with abdominal B-ultrasound in week 12 from the baseline.

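### A single-visit Wilcoxon rank-sum test is offered as an equal alternative to the mixed model for secondary outcomes measured at five follow-up visits; one baseline-adjusted repeated-measures model should be the main analysis (minor)

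*Protocol article*

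**What the plan says.** In the protocol article, under Statistical analysis, the method for repeated continuous outcomes is given in one sentence: "A mixed-effect model or Wilcoxon rank-sum test will be used to assess the longitudinal continuous variables". No condition is attached to either method.

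The Secondary outcomes section and Table 1 show what the sentence covers. The voiding-diary measures, ICIQ SF and OAB-q SF are all assessed at weeks 4, 8, 12, 24 and 36 after baseline.

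The Statistical analysis section adds three relevant statements:
- On missing data: "Missing data will be imputed using the multiple imputation method under the missing-at random assumption". This comes directly after the sentence on the primary analysis sets and names no outcome.
- On the analysis set: "Secondary and safety outcomes will be assessed in ITT populations". ITT is defined there as randomized participants.
- On status: "Since all analyses other than the primary analysis are considered descriptive, no adjustments will be made for multiple testing".

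Study design gives 94 women per arm, and Sample size calculation expects 10% dropout.

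**The concern.** The two methods are presented as interchangeable, but they do different things with these data.

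- **Structure.** A rank-sum test takes one value per woman and two arms. With three arms and five visits that is 3 × 5 = 15 separate tests per outcome, none of which uses the other visits.
- **Adjustment.** The test uses neither the baseline value nor centre, although randomization is stratified by centre. A mixed model can include both.
- **Missing values.** On observed data the test drops a woman with no value at that visit, whatever her earlier visits show. A mixed model keeps those earlier visits.
- **Imputation.** If multiple imputation extends to these outcomes, the rank statistic and its P value do not go directly into Rubin's rules. An estimate with a standard error is needed, and the article names none.

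The document gives reason to think that dropout could differ by arm. Solifenacin patients are not blinded and are treated for 36 weeks, whereas acupuncture ends at week 12. The Background section also reports side effects and frequent discontinuation for solifenacin. Stopping a drug is not the same as leaving the study, but arm-specific dropout is plausible. At stake are the precision, and possibly the validity, of the secondary comparisons out to week 36.

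**Working it through.** The plan states no figure on this point, so there is none to reproduce. The enrolment numbers are consistent: 3 × 94 = 282 and 42 + 5 × 48 = 282.

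**Inputs from the document:** 94 per arm, 10% dropout, five post-baseline visits, two-sided 5% level.

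**Assumed, because the document does not give them:** normal outcomes, between-visit correlation ρ of 0.5 to 0.7, the dropout mechanism, any dropout rate other than 10%, and the effect sizes.

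**Step 1. False-positive rate at week 36, no true difference.** The rank-sum test on observed values was simulated under several dropout mechanisms.

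| Dropout assumption | Rank-sum, observed values | Comparison |
|---|---|---|
| Depends on earlier result in the same way in both arms, 10% each | about 4–6% | likelihood analysis using earlier visits: 5.6–5.8% |
| Depends on week-12 result in one arm (logit slope 1.5 per SD), random in the other, 10% | about 6–8% | likelihood: 4–5% |
| Same as the row above, 20% | about 9–17% | likelihood: 4–5% |
| One-arm mechanism, with 10 within-arm imputations from week 12 and the Mann-Whitney estimate pooled by Rubin's rules | 4.8–5.0% at 10%, 4.9–5.0% at 20% | – |
| Opposite mechanisms in the two arms, driven by week 24 (slope 2 per SD), 10% each | 14–25% | likelihood: about 5% |

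In the one-arm scenario the bias is 0.06–0.09 SD at 10% dropout and 0.12–0.16 SD at 20%. The last row is an extreme case. The likelihood analysis is a per-arm regression on earlier visits and stands in for the mixed model.

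**Step 2. Power when dropout is unequal.** With 5% versus 15% dropout, the same mechanism in both arms and a true difference of 0.45 SD, power is 68–71% for the rank-sum test and 84–86% for the likelihood analysis. With 10% in each arm and the same mechanism, the two are close: 80–83% and 82–84%.

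**Step 3. Power with harmless dropout.** Take 10% random dropout and a difference of 0.4 SD, so n = 94 × 0.9 = 84.6 per arm. Power is Φ(δ − 1.96) with δ = 0.4 / √(2f / 84.6), where f is the variance factor.
- Rank-sum on raw values: efficiency 3/π = 0.955, so f = 1/0.955 = 1.047, δ = 2.54, power 72%.
- Baseline-adjusted: f = 1 − ρ². At ρ = 0.5, f = 0.75, δ = 3.00, power 85%. At ρ = 0.7, f = 0.51, δ = 3.64, power 95%.
- Rank-sum on change from baseline: f = 2(1 − ρ) × 1.047. At ρ = 0.5, f = 1.047, power 72%. At ρ = 0.7, f = 0.628, δ = 3.28, power 91%.

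Simulation gave about 73% for the rank-sum test on raw values and 86–95% for an analysis adjusted for baseline and earlier visits, in line with the formula. The third bullet matters because the Abstract describes secondary outcomes as changes. On change scores the gap stays at about 13 points at ρ = 0.5 (85 − 72) but shrinks to about 4 points at ρ = 0.7 (95 − 91).

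**The case against.** The best defence is that this is shorthand in a condensed article. The same section pairs other methods with an 'or' (generalized linear model or logistic regression, chi-square or Fisher's exact test). A natural reading is a model with a non-parametric fallback for skewed data, the trigger being left to an analysis plan that is not shown. That stands as far as it goes: the absence of a rule for choosing is not the finding. The finding is that one of the two named methods is a poorer main analysis for these data.

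A reader might infer several stronger points that the documents do not support:
- **That the rank-sum test is valid only if dropout is unrelated to earlier results.** When dropout follows the same mechanism in both arms, the null rejection rate stays near 5%. Harm needs a difference between arms.
- **That the bias applies under the plan as written.** The imputation sentence is not restricted to the primary outcome. If it covers these outcomes and uses earlier visits, the inflation goes away, and pooling is possible through an estimate with a standard error. The bias and pooling arguments need opposite premises about imputation, so they cannot be added together.
- **That no effect size would be available.** A Hodges-Lehmann shift with its interval, or arm means, can accompany the P value, and nothing in the section limits reporting to P values.
- **That the 'or' licenses taking the smaller P value.** The plan does not propose this, and its statisticians are blinded to allocation.

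Rank methods also have a real attraction for three-day diary counts, which are likely to be skewed.

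**Conclusion.** The concern holds in limited form. The text puts a two-arm, single-visit, unadjusted test on a par with a repeated-measures model for outcomes collected at five visits. The firmest cost is precision: about 73% against 86–95% power at 0.4 SD on raw values, and less if change scores are tested. The protection against arm-specific dropout is conditional. It matters only if these outcomes are not imputed from earlier visits and dropout depends on earlier results differently by arm. The false-positive rate is then about 6–8% at the plan's 10% dropout; the 9–17% range needs 20%, a rate that the document does not give. All these figures rest on assumed correlations, mechanisms and normal outcomes.

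Severity is minor. The outcomes are secondary and declared descriptive, and the primary retention-of-effect test does not depend on this sentence.

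**What to change.** Under Statistical analysis, replace the two-way choice with one main method: a mixed model for repeated measures for every longitudinal continuous outcome, with arm, visit, arm-by-visit interaction, baseline value and centre. Report the arm difference with a 95% confidence interval at each visit.

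Keep the rank-sum test only as a per-visit sensitivity analysis for skewed diary counts, with a Hodges-Lehmann shift and its confidence interval.

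The cost is wording and programming. No new data are needed, because the baseline value, centre and all five visits are already collected. The small downside is reliance on a model for skewed counts, which the sensitivity analysis is there to check. Recruitment has started, so the change should be made before unblinded data are seen.
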